## Abstract

**Background:** Hyponatremia is the most common electrolyte disorder with a prevalence of up to 30% in hospitalized patients. In contrast to acute hyponatremia where the need for immediate treatment is well-recognized, chronic hyponatremia is often considered not clinically relevant. This is illustrated by reports showing that appropriate laboratory tests are ordered in <50% of patients and that up to 75% are still hyponatremic at discharge. At the same time, emerging evidence suggests an association between hyponatremia and adverse events including increased risk of mortality and rehospitalization.

**Methods:** This is a randomized (1:1 ratio) controlled, superiority, parallel-group international multi-center trial with blinded outcome assessment. In total 2,278 participants will be enrolled. Participants will be randomly assigned to undergo either targeted correction of plasma sodium levels or standard of care during hospitalization. The primary outcome is the combined risk of death or re-hospitalization within 30 days.

**Discussion:** All data on hyponatremia and mortality are derived from observational studies and often lack methodologic robustness. Consequently, the direct impact of hyponatremia on mortality and rehospitalization risk is still debated, resulting in a clinical equipoise whether in-hospital chronic hyponatremia should be treated or not. Therefore, a randomized controlled trial is required to study whether targeted plasma sodium correction reduces the risk of mortality and rehospitalization associated with hyponatremia.

**Clinical Trial Registration:**www.ClinicalTrials.gov, identifier: NCT03557957.

## Background

Hyponatremia is the most common electrolyte disorder with a prevalence of up to 30% in hospitalized patients (1). In contrast to acute hyponatremia where the need for immediate treatment is well-recognized due to severe clinical symptoms caused by cerebral edema (2, 3), chronic hyponatremia is often considered not clinically relevant (4). A registry analysis from 225 sites in the European Union and the United States showed that appropriate laboratory tests to evaluate the etiology of hyponatremia were obtained in <50% of patients and up to 75% of patients was still hyponatremic at discharge (5).

However, there is increasing evidence showing an association between chronic hyponatremia and clinical complications including gait alterations, attention deficits, falls (6), bone loss, and fractures (7). Furthermore, hyponatremia is associated with worse prognosis in patients with heart failure (8–10), myocardial infarction (11, 12), liver cirrhosis (13), pneumonia (14), pulmonary embolism (15), chronic kidney disease (16) and in patients admitted to the intensive care unit (17). The increased risk of mortality that arises from several observational studies might result from an intricate combination of factors, including the underlying condition and concomitant diseases (18–20). Whether these associations indicate a causal relationship has not been established yet. The debate on whether hyponatremia contributes directly to mortality or is rather a surrogate marker for the severity of the underlying condition is ongoing (21).

Several studies have shown differences in neurocognitive and muscular function (6, 22), as well as an improvement in quality of life (23) and a reduction in costs through hyponatremia treatment (24). The key question, however,—whether targeted correction of hyponatremia reduces the risk of mortality and rehospitalization—has not been addressed. All data regarding hyponatremia and mortality originate from observational studies or retrospective analyses (25–27). A meta-analysis of fifteen observational studies with a total of 13,816 patients reported that any improvement of hyponatremia was associated with a reduced risk of overall mortality (OR 0.57; 95% CI 0.40–0.81) (26). Randomized controlled trials studying the effect of hyponatremia treatment on mortality were limited to studies assessing the effect of one drug class only: vaptans. Furthermore, inclusion was restricted to patients with either hyper- or euvolemic hyponatremia. Treatment with tolvaptan corrected hyponatremia, yet no difference in 30-day mortality between tolvaptan and placebo was found (28). Other small randomized controlled trials (*n* = 20–60) with vaptans reported similar outcomes (29–31). However, the results from these studies cannot be generalized to other treatment forms of hyponatremia, as vaptans bear the risk of overcorrection (32), which in turn can have serious neurologic ramifications including osmotic demyelination syndrome (33–35). Hyponatremia is a heterogeneous and complex disorder which may be best managed through a tailored approach with individualized treatment, rather than by applying a single treatment modality.

Except for the vaptan-trials, which cannot be extrapolated to the heterogeneous in-hospital hyponatremic population, there is a complete lack of randomized controlled trials investigating whether treatment of hyponatremia reduces the risk of mortality and rehospitalization associated with hyponatremia. To address this question, the aim of this international multi-center randomized controlled trial is to determine the benefits and harms of targeted hyponatremia correction on the combined endpoint 30-day mortality and rehospitalization rate.

## Methods

### Study Design

HIT is a randomized (1:1 ratio) controlled, superiority, parallel-group international multi-center study with blinded outcome assessment.

2,278 hospitalized patients with hypotonic hyponatremia <130 mmol/l will be includedParticipants will be randomly assigned to undergo either targeted correction of hyponatremia in addition to current standard care or current standard care during the course of the index hospitalizationThe primary outcome is assessed 30 days after inclusionOutcome assessment at 30 days and 1 year will be blinded to treatment allocation.

The study design flowchart is depicted in Figure 1.

**Figure 1 F1:**
[figure not shown]
Study design flowchart.

A detailed overview of study procedures and assessments during index hospitalization, at 30 days and 1 year is included in Supplementary Table 1.

### Eligibility Criteria

See Table 1 for the inclusion and exclusion criteria.

**Table 1 T1:** Inclusion and exclusion criteria.

**Inclusion criteria**	**Exclusion criteria**
All adult hospitalized patients with hypotonic hyponatremia <130 mmol/l	Severe symptomatic hyponatremia in need of intensive care treatment and/or of acute correction with 3% saline
Informed Consent as documented by signature	Non-hypotonic hyponatremia with plasma osmolality >300 mOsm/kg or in absence of plasma osmolality but with any circumstances suggestive of non-hypotonic hyponatremia End of life care
	Kidney failure requiring dialysis
	Acute liver failure
	Wernicke encephalopathy
	Hepatic encephalopathy during the last 2 months
	Hepatorenal syndrome
	Patients in the isolation ward due to hematological diseases
	Pregnancy/breastfeeding

### Screening and Recruitment

To enable a daily screening of all hospitalized patients, plasma sodium values ordered through regular care will be screened using an electronic alert system by the local study physician.

Patients will be contacted as soon as the diagnosis of hypotonic hyponatremia <130 mmol/l is established. Patients may be eligible for study participation at any time during their hospitalization.

### Randomization

Participants will be randomly 1:1 assigned to either the targeted-sodium-correction group or the standard treatment group. Randomization will be performed by the online database system SecuTrial®, stratified by study site and using permuted block of random sizes. The allocation sequence will be implemented by the study data manager of the clinical trial unit Basel, Switzerland. Randomization will be done directly after inclusion of each patient in the online database system.

### Blinding

Attempts to blind the hyponatremia interventions would create an artificial care environment with a substantial deviation from routine care. To minimize the risk of bias for the outcome assessment, outcome assessors are not involved in the study and are not aware of the treatment allocation. All outcome data will be entered into a separate database with no link to other study data.

### Study Intervention

#### A. Intervention Group

The recommended algorithm for diagnosing and treating hyponatremia is based on the current *European Clinical Practice Guidelines (ECPG)(2)* and the *Expert Panel Recommendations (EPR)(3)*. The study group will check for guideline updates regularly during the course of the study and if applicable amend the algorithm accordingly. The local study task force will be trained in the recommended diagnostic classification and treatment procedure prior to start of the study.

1. **Diagnosis:**Diagnosis of hyponatremia will be made by the local study physician and will be reviewed by the local principal investigator. According to the *ECPG*, patients will be classified into the 3 main groups of hypotonic hyponatremia (decreased/normal/increased extracellular fluid volume; details see Supplementary Figure 1). If the diagnosis is uncertain, the most likely categorization will be chosen. This initial diagnosis can and shall be changed according to treatment response and/or additional clinical information. The final diagnosis will be made before the patient is discharged.2. **Treatment:**The proposed treatment recommendation will be based on the predefined algorithms which were developed in accordance to the ECPG(2) and the EPR(3) (details see Supplementary Figure 2). The treatment algorithm is a recommendation only, meaning the proposed algorithm is intended as a guideline rather than a strict treatment plan. This approach takes into account the sometimes limited data for certain treatments (36) and enables the local expert to decide upon the best treatment for every patient individually based on the available treatment options. Given that the hyponatremia patient population in clinical practice is very heterogeneous, we decided a tailored approach for hyponatremia correction would be in the best interest of the patients. Except for correction of hyponatremia, the local study team will not influence other treatment goals and decisions, which will be fully at the discretion of the attending physicians. Treatment response and adherence will be evaluated daily. The study nurse will report to the study physician, who will additionally examine the patient if clinically indicated. The study physician will then—under the supervision of the local principal investigator—adapt treatment recommendation according to the predefined treatment goals and inform the treating physicians about the treatment modification. The general treatment goal is to raise plasma sodium levels by at least 2 mmol/l/24 h. These treatment goals also define the time until the next treatment step should be implemented. The following management rules apply:increase ≥2 mmol/l/24 h and <12 mmol/l/24 h and 18 mmol/l/48 h: current treatment option will be maintained until plasma sodium level has normalizedincrease <2 mmol/l/24 h: treatment will be intensified or switched to a different modalityincrease >12 mmol/l/24 h and/or 18 mmol/l/48 h: treatment will be discontinued and, if needed, counter regulatory actions (i.e., hypotonic infusion, administration of desmopressin) will be administered according to the decision of the local principal investigator.

Episodes of overcorrection (defined as increase >12 mmol/l/24 h, respectively 18 mmol/l /48 h) and their complications will be recorded. Targeted plasma sodium correction will be maintained—for a maximum of 30 days—until normonatremia is achieved or when the patient is discharged from hospital. At discharge the last available plasma sodium level and whether or not patient was treated according to protocol will be recorded. Not treated according to protocol applies in the case treatment recommendation is not implemented or the patient does not adhere to the prescribed treatment (details see below “Compliance with study intervention”). In case of hospitalization exceeding 30 days, the last plasma sodium level before stopping the intervention (day 31) will be recorded as the discharge plasma sodium. Treatment after discharge will not be influenced by the study team, however a treatment recommendation and request to monitor plasma sodium levels will be given to the general practitioner in the discharge letter.

#### B. Control Group (Standard Care)

##### 1. Diagnosis

Laboratory analysis (blood and urine samples) to diagnose hyponatremia will be at the discretion of the attending physician according to local standards of care. The final hyponatremia diagnosis will be made by the study team at discharge according to all available clinical and laboratory information as well as treatment response.

##### 2. Treatment

Treatment of hyponatremia will be solely at the discretion of the attending physicians. The study team will not intervene with the treatment in any way. Treatment decisions as well as the course of the plasma sodium level will be recorded after patient is discharged from hospital using the medical records and patient charts. To ensure the planned outcome assessment, it will be generally recommended to measure plasma sodium levels 3 times weekly or more frequently if clinically indicated, before discharge and after 30 days.

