##### Compliance With Study Intervention in Both Study Groups

Adherence will be evaluated as follows:

(A) Intervention group:

Administration of the prescribed treatment will be monitored daily through visits on the hospital ward by the local study nurse.Treatment response will be monitored daily for a maximum of 30 days by the study physician and treatment will be adjusted accordingly.

(B) Control group (standard care):

Diagnostic evaluations, plasma sodium levels and prescribed treatment will be recorded by the local study nurse through evaluation of the patient-chart and laboratory values after patient is discharged from hospital.The study team will not contact or advise the attending physicians in any way.

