### Objectives and Outcomes

#### Objectives

The primary objective is to investigate whether in hospitalized hyponatremic patients targeted correction of plasma sodium concentration plus standard care compared to standard care alone reduces the combined 30-day risk of mortality or rehospitalization. The secondary objective is to investigate whether the intervention has favorable effects on other patient relevant outcomes. Lastly, the study aims to assess the tolerability and risks of targeted correction of plasma sodium concentration.

See Supplementary Table 2 for the complete set of outcomes.

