#### Secondary Analysis

Each of the components of the primary outcome, death and rehospitalization, will be analyzed separately as described for the primary outcome. Time to death and rehospitalization after 30 days and 1 year will be analyzed by fitting Cox proportional hazards regression models with trial arm as explanatory variable. Hazard ratios including their confidence intervals will be reported. Patients will be censored on their last known follow-up. To illustrate the course of deaths and re-hospitalizations in the two treatment arms, a Kaplan-Meier Curve will be presented.

Length of hospital stay will be calculated in days considering index and each rehospitalization separately and by the sum of all hospital stays. Standard summary statistics for numerical data will be performed. If distribution of data allows, significant differences of mean of length of hospital stay between arms will be assessed with a *t*-test (two-sided α = 5%). If distribution is skewed, data will be transformed or other models selected.

The secondary outcomes (falls, fractures, course of hyponatremia, recurrence of hyponatremia, severe symptomatic hyponatremia, overcorrection of hyponatremia) will be analyzed as described for the primary outcome. To account for multiple occurrences of falls, fractures, and recurrence of hyponatremia after 1 year, we will apply a Poisson model.

Diagnostic performance of biomarkers will be assessed by calculating sensitivity, specificity and accuracy as well as best cut-offs. Gold standard is the correct diagnosis of etiology of hyponatremia, which is expert opinion based on biochemistry results and treatment response.

Analyses of differences of quality of life score and of executive functioning score between arms will be performed also considering grade of hyponatremia and its correction. Multivariate linear models will be used to explore possible associations.

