### Safety Analysis

Incidence rates of AE/SAE, including symptomatic hyponatremia and plasma sodium overcorrection during index hospitalization, will be calculated at study end as described for the primary outcome. Summary statistics of multiple occurrences of AE/SAE within individual patients, will be presented separately. An independent data safety monitoring board will oversee the trial and conduct a safety-analysis after 1,000 patients have completed the 30-day follow-up.

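### Overcorrection is compared between arms by the primary chi-square test although sodium is probably followed more closely under targeted correction, so the comparison is likely biased against the intervention

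*Protocol article*

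**What the plan says.** All references are to the protocol article.

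- **Definition** (Study Intervention, A. Intervention Group): "Episodes of overcorrection (defined as increase >12 mmol/l/24 h, respectively 18 mmol/l /48 h) and their complications will be recorded".
- **Intervention arm** (same section): "Treatment response and adherence will be evaluated daily". The management rules keep, intensify or stop treatment according to the rise per 24 h, with an upper limit also at 48 h. The compliance section adds: "Treatment response will be monitored daily for a maximum of 30 days by the study physician".
- **Control arm** (B. Control Group, 2. Treatment): "it will be generally recommended to measure plasma sodium levels 3 times weekly or more frequently if clinically indicated, before discharge and after 30 days". The sodium course is taken from records and charts after discharge.
- **Analysis** (Secondary Analysis): "recurrence of hyponatremia, severe symptomatic hyponatremia, overcorrection of hyponatremia) will be analyzed as described for the primary outcome". The Safety Analysis section treats adverse events the same way, "including symptomatic hyponatremia and plasma sodium overcorrection during index hospitalization, will be calculated at study end as described for the primary outcome". Under Primary Analysis, that method is the Pearson chi-square test without Yates's correction at 5%, with the absolute difference and its 95% confidence interval.
- **Aim** (Objectives): "Lastly, the study aims to assess the tolerability and risks of targeted correction of plasma sodium concentration".

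**The concern.** Whether a patient counts as overcorrected depends on having two sodium values close enough together. The article ties the intervention arm to a 24 h rhythm and gives the control arm only a recommended minimum of three values a week. The same sodium course can then be an event in one arm and go uncounted in the other, yet the planned test reads any difference in counts as a difference in risk.

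Overcorrection is the main harm that the Background section attaches to active treatment, and assessing the risks of the strategy is a stated aim. With equal true risk, the planned test would tend to show an excess under targeted correction. If the risk really is higher, the excess could not be separated from the effect of closer measurement. If the stopping rules really lower the risk, that benefit could be masked.

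**Working it through.** **1. The plan's own figure.** For 23% versus 18%, two-sided 5% and 80% power, the uncorrected chi-square formula gives 1,023 per arm, 2,046 in total. The article states 2,050 evaluable, and 2,050 / 0.90 = 2,278 recruited. The sample size reproduces and is not in dispute. I use 2,050 / 2 = 1,025 per arm below.

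**2. Why sparse values miss events.** Three values a week are on average 7 / 3 = 2.3 days apart. Suppose a patient rises 13 mmol/l on one day and then levels off.
- With daily values: 13 > 12 mmol/l in 24 h, so an event.
- With values 48 h apart: 13 < 18 mmol/l in 48 h, so no event.

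**3. Chance of a false excess.** Let p be the risk as seen with daily values, equal in both arms. Let r be relative detection, the share of those cases that control sampling also finds. Neither is in the article; both are assumptions. The observed risks are p (intervention) and r·p (control). With n = 1,025 and m = p(1 + r)/2:

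P(significant excess) = Φ{ [p(1 − r) − 1.96·√(2m(1 − m)/n)] / √([p(1 − p) + rp(1 − rp)]/n) }

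For p = 5% and r = 0.80: difference 0.010, m = 0.045, null SE 0.00916, alternative SE 0.00916. So (0.010 − 0.01795) / 0.00916 = −0.87, and Φ = 0.19.

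| r | p = 3% | p = 5% | p = 8% |
|---|---|---|---|
| 1.00 | 2.5% | 2.5% | 2.5% |
| 0.93 | 5% | 6% | 7% |
| 0.90 | 6% | 8% | 10% |
| 0.80 | 13% | 19% | 29% |
| 0.75 | 18% | 28% | 43% |
| 0.50 | 63% | 85% | 97% |

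At p = 5% the chance passes 10% once r is about 0.87 or lower.

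**4. Which r is plausible?** This was simulated under an assumed model: the same daily sodium changes in both arms (mean 2–3, SD 4–5 mmol/l), start 115–130, cap 140, first and pre-discharge values always taken, Monday/Wednesday/Friday values plus the extra tests shown. The shorter stays and the near-daily row used mean 3 and SD 4.

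| Extra control testing | Days | r |
|---|---|---|
| None | 7 | 0.24–0.28 |
| Next-day test with 80% chance if last value <125 | 7 | 0.62–0.65 |
| As above, plus 50% chance on any day | 7 | 0.80–0.82 |
| As above, plus 50% chance on any day | 3 | 0.87 |
| As above, plus 50% chance on any day | 2 | 0.93 |
| Near daily (95% and 80%) | 2–7 | 0.93–0.98 |

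The first row leaves out the clause allowing more frequent tests when indicated, so it is only an outer limit. The other rows run from a substantial bias to a small one.

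**The case against.** **The premise is inferred.** No sentence in the article says how often blood is drawn in the intervention arm, and the schedule of assessments and treatment algorithm are in supplements that are not shown. This stands as a caveat: a reader might infer that daily sampling is prescribed, and the text does not say so. But daily decisions on a per-24 h rise can hardly be made without roughly daily values.

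**Control sampling is a floor.** Inpatients with very low sodium on active treatment are the likeliest both to overcorrect and to be tested more often. Stays may also be short. This stands, and it means that detection could be near equal. It narrows the gap without closing it by design.

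**The clinical harm is protected.** Complications such as osmotic demyelination are sought in both arms by staff blinded to allocation. This also stands: what is distorted is mainly the biochemical event. That event is nevertheless tested in its own right in two sections.

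**The trade-off is disclosed.** The Discussion admits a tension between contaminating standard care and complete data. It does not mention what this does to the overcorrection comparison. Accepting sparser control sampling is reasonable; testing the resulting counts as if sampling were equal does not follow from it.

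**Stopping rules may prevent overcorrection.** If so, that is a real treatment effect, and it does not offset unequal detection.

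**Conclusion.** The point holds. Following the text as written probably gives unequal detection of overcorrection, with the bias against the intervention. The direction is firm provided intervention sodium is measured more often than control sodium. The size is not: at an assumed 5% risk and 1,025 per arm, the false-excess chance is about 6% at 93% relative detection, 19% at 80% and 85% at 50%, against 2.5% nominal. It is small if controls are tested almost daily and large if they are tested near the recommended minimum.

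Two stronger readings are not supported. One is that a false excess is nearly certain; that needs controls tested three times a week and no more, which the article does not say. The other is that the trial's main conclusion or its whole safety assessment is compromised. Death and rehospitalization do not depend on sodium sampling, and complications assessed at blinded follow-up are less affected. The fault lies in how one secondary and safety outcome is tested, and it is worth correcting before analysis.

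**What to change.** Amend Secondary Analysis and Safety Analysis as follows.

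1. Report the full overcorrection count by arm from all available values, with the estimated difference and 95% confidence interval but no confirmatory test. Show sodium measurements per patient-day by arm beside it.
2. State that unequal sampling can by itself produce an excess under targeted correction, and that the interval does not allow for this.
3. Add a sensitivity analysis that applies the same 24 h and 48 h criteria to intervention values thinned to the sampling observed in controls. Thin by the daily chance of a value given the last sodium and the days since it. Fix the random seed and repeat the thinning.

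In simulation (mean 3, SD 4, equal true risk, first three control patterns in the second table over 7 days), thinning brought the false-excess chance from 0.998, 0.55 and 0.17 to 0.035, 0.018 and 0.019. That check used the same variables that drove testing in the model, so it is partly circular, which is one reason to keep thinning as a sensitivity analysis.

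**Cost.** A short text change and no extra blood draws, since control values are already collected from charts. There is no confirmatory p-value for overcorrection. The sensitivity analysis loses power: for a real excess of 8.1% versus 4.6%, from 87–90% with daily values in both arms to 81%, 71% or 44% as control sampling gets sparser. Tests prompted by symptoms or by starting treatment leave some residual difference.

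As a separate editorial matter, the compliance section says of controls "The study team will not contact or advise the attending physicians in any way", which should except the general recommendation on sodium measurement.
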